### Analysis

All data will be analysed according to intention-to-treat principle. Means, standard deviations will be used to summarise overall and within subgroups defined by the range of medical, sociological, and other risk factors collected at baseline. Mean scores of POMS, STAI and CASE-cancer will be compared initially across intervention and control groups using ANOVA (repeated measures) to analyse the effect between groups over time (or Friedman test if normality is not a valid assumption). Success of randomisation will then be considered by cross-tabulating trial group with the range of factors. Any found to be in substantial imbalance will be included in multivariable linear regression models, via forced entry, to adjust the crude means and these will be reported with 95% confidence intervals. Analyses will use the SPSS (Version 16) package and a generalised linear modelling framework.

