**Methods:**

The concept of interventions for orienting new cancer patients needs revisiting due to the dynamic health care system. Historically, most orientation programs at this cancer centre were conducted by one nurse. A randomised controlled trial has been designed to test the effectiveness of an orientation program with bundled interventions; a face-to-face program which includes introduction to the hospital facilities, introduction to the multi-disciplinary team and an overview of treatment side effects and self care strategies. The aim is to orientate patients to the cancer centre and to meet the health care team. We hypothesize that patients who receive this orientation will experience lower levels of anxiety and distress, and a higher level of self-efficacy.

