### Study population

All cancer patients newly registered at a tertiary cancer care centre in Brisbane, Australia, who meet inclusion criteria will be invited to participate in the trial. Patients who consent will be randomly allocated to either the control group, who will receive normal treatment education at the start of their treatment, or the intervention group, who will receive the normal treatment education and will also attend the Orientation Program education session conducted by the multi-disciplinary team, prior to starting their treatment.

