#### Allocation concealment/implementation

After the research nurse has obtained the patient's consent, he/she will telephone a contact who is independent of the recruitment process for allocation concealment. Subsequently, baseline data will be collected. All questionnaires are self-administered by patients. Therefore, the research nurse will not have involvement in completing these questionnaires.

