### Data collection

Participants will be asked to complete a series of questionnaires at the time of recruitment (T1), on the day of first treatment (T2), and on the seventh day of treatment (T3) which will measure patients' self-efficacy (CASE) and anxiety (STAI and POMS) at the three time points. Additionally, demographic information will be collected at T1 and the EOCQ will be collected at T2 and T3.

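### The repeated-measures ANOVA over T1 to T3 is valid but targets the hypothesis inefficiently; a 1-df comparison of the T2/T3 mean adjusted for T1 would serve it better

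*Protocol article*

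**What the plan says.** The Analysis section says that mean POMS, STAI and CASE-cancer scores will be "compared initially across intervention and control groups using ANOVA (repeated measures) to analyse the effect between groups over time". It does not say whether the group term or the group-by-time term is the test, and it names no contrast or time point. The T1 score is not named as a covariate. The later regression takes in baseline factors only if they look unbalanced: "Any found to be in substantial imbalance will be included in multivariable linear regression models, via forced entry, to adjust the crude means".

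The Data collection section measures "patients' self-efficacy (CASE) and anxiety (STAI and POMS) at the three time points". T1 is at recruitment, T2 on the first treatment day and T3 on the seventh day of treatment. The Study population section says intervention patients "will also attend the Orientation Program education session conducted by the multi-disciplinary team, prior to starting their treatment", so the program falls after T1 and before T2.

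The abstract gives the hypothesis a direction: "patients who receive this orientation will experience lower levels of anxiety and distress, and a higher level of self-efficacy".

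**The concern.** The hypothesis is about score levels after the program. T1 is taken before it, so the program itself cannot have acted by then. The article does not state outright that T1 is an ANOVA level, but three measurement times and an analysis over time are most naturally read that way.

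Two terms in such an ANOVA involve arm:

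- The group main effect compares the arms on the average of T1, T2 and T3, and one third of that average is pre-program.
- The group-by-time interaction asks whether the three-point profiles are parallel. It has 2 df, responds equally to benefit and to harm of the same size, and does not reduce to one signed number.

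What is at stake is power and ease of interpretation. Under no effect, both tests keep their nominal type I error.

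**Working it through.** **Inputs from the article.** Three times per patient (Data collection); 375 per arm, 90% power and 95% confidence, with a pilot of 51 per arm (Sample size and power); STAI test-retest correlations of 0.65 to 0.86 (Measures, Anxiety).

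**Assumptions.** Two-sided 0.05; equal SDs, scaled to 1; compound symmetry with correlation ρ; arm effects (0, d, d) at T1, T2 and T3. No ρ is given for this trial, so 0.5 to 0.86 is used, which covers the quoted reliability range.

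**The plan's own figure.** No difference or SD is stated, so 375 per arm cannot be reproduced. Read as a simple comparison of two means, it corresponds to d = √(2/375) × (1.960 + 1.282) = 0.237 SD.

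**Dilution.** The main effect estimates (0 + d + d)/3 = 2d/3. At 0.237 SD that is 0.158 SD. This step needs no value of ρ.

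**Noncentrality, n per arm.**

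- Main effect: λ = (n/2)(2d/3)² / [(1 + 2ρ)/3], df 1 and 2n − 2
- Interaction: λ = (n/2)(2d²/3)/(1 − ρ), df 2 and 2(2n − 2)
- T2/T3 mean minus T1, 1 df: λ = (n/2)d² / [1.5(1 − ρ)], which equals the interaction's λ
- T2/T3 mean adjusted for T1, 1 df: λ = (n/2)d² / [(1 + ρ)/2 − ρ²]
- T2/T3 mean unadjusted, 1 df: λ = (n/2)d² / [(1 + ρ)/2]

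Worked case, n = 375 and ρ = 0.5. The adjusted comparison has 90% power at d = 0.168. Its λ is 10.53, against 7.02 for the interaction and 3.51 for the main effect.

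**Power at the d where the T1-adjusted comparison has 0.90 (n = 375).**

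| ρ | 0.5 | 0.65 | 0.70 | 0.86 |
|---|---|---|---|---|
| d (SD) | 0.168 | 0.150 | 0.142 | 0.103 |
| Main effect | 0.465 | 0.347 | 0.305 | 0.168 |
| Interaction, 2 df | 0.656 | 0.721 | 0.740 | 0.795 |
| T2/T3 mean minus T1, 1 df | 0.754 | 0.810 | 0.826 | 0.870 |
| T2/T3 mean, unadjusted | 0.75 | 0.62 | 0.56 | 0.31 |

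With 51 per arm, and d re-solved for that size, the powers are nearly the same.

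**Where the loss comes from.** The change contrast and the interaction share one λ, so the gap between them is the price of the second degree of freedom: 0.754 − 0.656 = 0.098 at ρ = 0.5, falling to 0.870 − 0.795 = 0.075 at ρ = 0.86. The rest of the interaction's shortfall (0.90 − 0.754 = 0.146 down to 0.90 − 0.870 = 0.030) comes from not using T1 as a covariate. For the main effect at ρ = 0.86, 0.90 − 0.31 = 0.59 is lost by not adjusting for T1, and only 0.31 − 0.17 = 0.14 by averaging T1 in.

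**Power at 0.237 SD, 375 per arm.**

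| ρ | 0.5 | 0.65 | 0.70 | 0.86 |
|---|---|---|---|---|
| Main effect | 0.753 | 0.693 | 0.675 | 0.620 |
| Interaction | 0.928 | 0.985 | 0.994 | >0.99 |
| T1-adjusted T2/T3 mean | 0.996 | 0.999 | >0.999 | >0.999 |

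**Effect at T2 only (0.237 SD, 375 per arm).** The adjusted T2/T3 mean has power 0.629 at ρ = 0.5 and 0.960 at ρ = 0.86; the interaction has 0.928 and above 0.99.

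**The case against.** A reader might infer that neither ANOVA test addresses the hypothesis. The article does not support that. Under randomisation the interaction's null is false whenever the hypothesised pattern (0, d, d) holds, and the main effect is valid though diluted. Two-sided testing is no defect, because direction can be read from the arm means that the plan will report.

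The wording about an effect over time points more to the interaction than to the main effect, so the largest losses attach to the less likely reading. Much of the loss also reflects the missing T1 adjustment, as the breakdown shows. The effect at which the adjusted comparison has exactly 90% power is a chosen benchmark; at 0.237 SD the interaction performs well. All of this stands, and it limits the point to efficiency and clarity.

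It can also be said that naming the tested term is left to a fuller plan, and that the current stage is a pilot. The first part is fair as to the missing term. But the article does commit to a method, and that method can be judged as stated. The pilot is meant to try out the design, so it is a good moment to settle the main comparison.

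Signed reporting is not wholly absent, since regression-adjusted means will carry 95% confidence intervals. That regression, however, depends on imbalance being found and does not name T1.

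**Conclusion.** The point holds as one of efficiency and interpretability; validity is not in question. With T1 as an outcome level, the main effect estimates two thirds of a constant post-program effect, and the interaction is a 2-df omnibus without a single signed estimate. Where a T1-adjusted comparison has 90% power, the interaction gives up 10 to 24 points, of which about 7 to 10 are due to the second degree of freedom. The main effect gives up 43 to 73 points.

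A reader might go further and expect a null result to be produced by the test alone. At 0.237 SD and 375 per arm that is not supported for the interaction, which has at least 93% power for ρ of 0.5 or more. It is a real risk only if the main effect is used (62 to 75%).

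The power figures depend on the assumed correlation, equal SDs, compound symmetry and equal effects at T2 and T3. The two-thirds dilution depends only on there being no effect at T1 and an equal effect at T2 and T3.

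One qualification concerns T1. The Allocation concealment/implementation section places the allocation call first and then says "Subsequently, baseline data will be collected", and the Blinding/masking section says patients cannot be blinded. T1 precedes the program, but knowledge of allocation could already have moved it.

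**What to change.** In the Analysis section, make the main comparison for POMS, STAI and CASE-cancer the 1-df arm difference in the mean of T2 and T3, adjusted for the T1 score as a covariate. Report it as a signed difference with a 95% CI, and give the T2 and T3 differences separately as secondary results. In Allocation concealment/implementation, have T1 completed before the allocation call, so that it is a clean baseline for this adjustment.

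The analysis change is wording only, with the same data and the same SPSS package. Its one statistical cost is lower sensitivity when the effect is present at only one of T2 and T3; the secondary estimates would show such a pattern. The timing change only reorders steps at recruitment.

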### Sample size and power

A sample size of at least 375 in each arm of the study would be sufficient to achieve a power of 90% using 95% of confidence interval to detect a difference in the anxiety and self-efficacy scores between control group and intervention group. Assuming that approximately 25% fail to consent and a further 10% will be lost to follow-up; an additional 132 in each group will be required and the final sample will require 1,014 patients. In order to evaluate the research design and process, the current proposal is for a pilot study with 10% of the final sample (ie 102 patients, 51 in each arm). According to the statistics of RBWH Cancer Care Services, 274 new cancer outpatients receiving treatment each month. Thus, the sample size proposed is achievable over a period of 12 weeks based on our conservative estimation.

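### As named, repeated-measures ANOVA (or Friedman) would drop every patient missing one questionnaire unless imputation is added, which fits poorly with the intention-to-treat statement

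*Protocol article*

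**What the plan says.** The Analysis section opens with the principle: "All data will be analysed according to intention-to-treat principle". It then names the comparison of POMS, STAI and CASE-cancer means between groups, "using ANOVA (repeated measures) to analyse the effect between groups over time", with a fallback: "or Friedman test if normality is not a valid assumption". Multivariable linear regression follows if baseline factors turn out to be substantially imbalanced. The section closes: "Analyses will use the SPSS (Version 16) package and a generalised linear modelling framework".

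The Data collection section sets three questionnaire times: recruitment (T1), the first treatment day (T2) and the seventh treatment day (T3).

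The Sample size and power section starts from "A sample size of at least 375 in each arm of the study" and allows for losses: "Assuming that approximately 25% fail to consent and a further 10% will be lost to follow-up". Its response to those losses is to recruit more patients. The article names no imputation, mixed model or generalised estimating equations.

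**The concern.** Classical repeated-measures ANOVA treats the three scores as one multivariate record. In its standard software form it deletes any patient whose record is incomplete. The Friedman test also needs complete blocks. A patient who returns T1 and T2 but not T3 therefore contributes nothing, although two scores were collected.

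Two things are at stake:

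- **Inclusion.** Patients stay in their assigned arm, so that part of intention to treat survives. What is lost is the inclusion of all randomised patients.
- **Bias.** Recruiting more patients restores numbers but does not correct a selective loss. The Blinding/masking section accepts that patients know their arm, and only the intervention arm meets the team before treatment. All outcomes are self-completed. Willingness to return a form could therefore depend on distress in one way in one arm and in another way in the other.

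**Working it through.** **1. The plan's own figure.** Adding the two allowances reproduces it: 375 × (1 + 0.25 + 0.10) = 506.25, rounded up to 507 per arm. Then 507 − 375 = 132 and 2 × 507 = 1,014, as stated. Ten per cent of 1,014 is 101.4, hence the pilot of 102 (51 per arm). The loss allowance enters only as extra recruitment.

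**2. Patients dropped in the pilot.**
- At 10% loss: 0.10 × 102 = 10.2, about 10 patients. This leaves 51 × 0.9 = 45.9, about 46 per arm.
- The number of T2 scores discarded is at most about 10, because the article does not say when loss occurs. A patient lost before T2 has no T2 score to discard.
- I take 102 as randomised, since it is given per arm. If it counted patients invited, 102 × 0.75 = 76.5 would be randomised and about 8 lost.
- If the 10% does not describe missing forms, the figure moves. With T2 and T3 each missed independently (assumed) at 5%, 1 − 0.95² = 9.75% are incomplete. At 10% each, 1 − 0.90² = 19%.

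**3. Precision and power.**
- Pilot standard error of a difference in means: √(2/51) = 0.198 SD with all patients and √(2/45.9) = 0.209 SD with completers, about 5% larger.
- The article gives no effect size. Back-calculating from 375 per arm, 90% power and two-sided 5% (sidedness assumed): (1.960 + 1.282) × √(2/375) = 0.237 SD.
- At 0.237 SD, a simple comparison of two means gives:

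| Per arm analysed | How it arises | Power |
|---|---|---|
| 375 | plan's target | 90% |
| 338 | 375 randomised, 10% lost | 86.8% |
| 342 | 507 invited, 25% decline, 10% lost | 87.2% |
| 456 | 507 randomised, 10% lost | above 90% |

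The power cost is at most about 3 points and may be nil, depending on what 507 counts.

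**4. Bias, illustration only.** Everything in this step is assumed: 500,000 simulated patients per arm, no true effect, correlation 0.5 or 0.7 between times, and drop-out after T2. Where drop-out depends on the score, its odds double per SD of the T2 score. The table gives the completers' difference in means (intervention minus control), for correlation 0.5 / 0.7.

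| Drop-out | T1 | T2 | T3 |
|---|---|---|---|
| 10% in both arms, same mechanism | 0.000 / −0.001 | −0.003 / 0.001 | −0.002 / 0.001 |
| 10% in both arms, score-related only in intervention | −0.032 / −0.047 | −0.069 / −0.064 | −0.035 / −0.046 |
| 5% control, 15% intervention, score-related in both | −0.037 / −0.047 | −0.068 / −0.065 | −0.036 / −0.049 |

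With one mechanism in both arms the bias is about zero. With differing mechanisms it is about 0.04 to 0.05 SD at T3 and about 0.07 SD at T2. T1 is displaced too, so part cancels in changes from T1. In the second row the T1-to-T2 change is off by −0.069 + 0.032 = −0.037 (correlation 0.5) or −0.064 + 0.047 = −0.017 (0.7). The T1-to-T3 change is off by 0.003 or less. The bias therefore also depends on which term of the ANOVA is read as the treatment effect.

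**The case against.** The strongest reply is that the article never says incomplete patients are excluded. A condensed article may leave missing-data handling to a fuller document, and repeated-measures ANOVA after imputation would agree with every sentence of the section. This stands. A reader might infer that the stated intention-to-treat analysis is really a completers analysis. The documents do not support that as a statement of fact. It is what the named method does if nothing is added.

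Further points that stand in part:

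- The ANOVA is only the initial comparison. The later regression need not require all three forms, but it is described only for adjusting imbalanced factors.
- The closing reference to a modelling framework could be stretched to cover generalised estimating equations. It is vague, and it does not replace the ANOVA named in the same section.
- Intention to treat can be read as analysis by assigned arm, which listwise deletion respects. On that reading the two statements sit uneasily together but do not flatly contradict each other.
- Extra recruitment already offsets some or all of the precision loss.

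A reader might also infer a sizeable bias. For example, if 15% against 5% drop out and drop-outs are 0.5 SD more anxious, (0.15 − 0.05) × 0.5 = 0.05 SD, which is 0.05/0.237 = 21% of the back-calculated effect. Both inputs are assumed. Nothing in the documents shows that the most distressed patients return fewer forms, or that the arms would differ.

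**Conclusion.** The concern holds in a limited form. The article fixes a method that, without imputation, drops every patient missing any one of three questionnaires. It does so beside an intention-to-treat commitment and its own expectation of 10% loss. This is a choice of method that the article makes, so it is more than a detail left unstated.

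At 10% loss the consequence is up to about 10 of 102 pilot patients excluded, with any T2 scores they gave. This assumes that 102 are randomised and that the 10% covers everyone with a missing form. The power cost is small. Bias is possible but cannot be sized from the documents: it is about zero if drop-out works alike in both arms. The simulated 0.04 to 0.07 SD at T2 and T3 under differing mechanisms is small against a pilot standard error of about 0.2 SD. The case for changing the method rests mainly on the full trial, which would inherit it.

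**What to change.** In the Analysis section, replace repeated-measures ANOVA with a likelihood-based linear mixed model for each score:

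- all available scores from all randomised patients, in the arm assigned;
- unstructured covariance over time, a group-by-time effect, and diagnosis stratum as covariate;
- T1 as a covariate only if it is completed before allocation is disclosed. The Allocation concealment/implementation section places baseline collection after the allocation call, and patients cannot be blinded, so this order needs settling first.

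The Friedman fallback has the same complete-record requirement and should be dropped or labelled complete-case.

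Add one sensitivity analysis that shifts missing scores by arm-specific amounts and covers patients with no post-baseline score. The mixed model alone cannot recover outcomes for patients lost before T2, so the main analysis would still rest on an assumption about them.

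If the ANOVA is kept without imputation, call it a complete-case analysis and do not present it as including all randomised patients.

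The cost is a change of wording and slightly more analysis work. No extra patients or questionnaires are needed, although using T1 as a covariate may mean collecting it earlier. The model assumes data are missing at random given the observed scores, and the sensitivity analysis is there to test that assumption.

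### The non-parametric fallback (Friedman test) ignores treatment arm, so it cannot test the between-arm hypothesis

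*Protocol article*

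**What the plan says.** The Analysis section sets out a comparison of the two arms on all three scales, "using ANOVA (repeated measures) to analyse the effect between groups over time". The parenthesis that follows gives the substitute: "or Friedman test if normality is not a valid assumption". No other non-parametric method is named.

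The rest of the article confirms that the question is between arms. Under Study population, "Patients who consent will be randomly allocated to either the control group, who will receive normal treatment education", with the orientation session added in the other arm. Under Data collection, each patient is measured three times: T1 (recruitment), T2 (first treatment day) and T3 (seventh treatment day). The Abstract gives the hypothesis: "We hypothesize that patients who receive this orientation will experience lower levels of anxiety and distress, and a higher level of self-efficacy".

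**The concern.** Friedman's test is the rank analogue of a one-group repeated-measures ANOVA. It is not the analogue of the two-group analysis it is meant to replace. If the normality check fails, the initial comparison turns into a test of whether scores change over time.

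A shared time trend is likely here. Patients are measured at recruitment and again on the first and seventh days of treatment, and the Background says anxiety can be especially marked at the first visit. The fallback could then give a highly significant result when the arms do not differ, or miss a real difference when the arms move in opposite directions. Running it once per arm does not help, because significance in one arm and not in the other is not a test of the difference between them.

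**Working it through.** **The statistic.** With N patients and k = 3 times, let R_j be the sum over patients of the within-patient rank at time j.

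Q = [12 / (N·k·(k+1))]·ΣR_j² − 3N(k+1) = (1/N)·ΣR_j² − 12N, referred to chi-square on 2 df. The 5% critical value is −2·ln(0.05) = 5.99.

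No arm label appears. Reassigning patients to arms in any way leaves Q unchanged.

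**Two extreme cases, n per arm, N = 2n.**
- Every intervention patient falls steadily (ranks 3, 2, 1) and every control patient rises (1, 2, 3), the largest possible arm difference in ranks. Each R_j = 4n, so Q = (3 × 16n²)/(2n) − 24n = 0.
- Every patient in both arms falls (3, 2, 1), so the arms do not differ. The R_j are 6n, 4n and 2n, so Q = (36 + 16 + 4)n²/(2n) − 24n = 4n. At the pilot's 51 per arm, Q = 204 against 5.99.

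**The plan's figures.** The 375 per arm in Sample size and power cannot be reproduced, because no effect size or SD is given. Back-solving for 90% power at two-sided 5% gives d = (1.960 + 1.282) × √(2/375) = 0.237 SD, used below as an assumed effect. The pilot has 51 per arm; less 10% loss this is 51 × 0.9 ≈ 46.

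**Simulation 1.** 2,000 runs, normal scores, assumed within-patient correlation 0.6; mean profiles (T1, T2, T3) in SD units are assumed. The comparator is a Mann-Whitney test of T3 − T1 change between arms.

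| Profile | n per arm | Friedman, all patients | Mann-Whitney on change |
|---|---|---|---|
| Both arms 0, −0.25, −0.40 (no effect) | 51 | 94% | 4.5% |
| Same | 375 | 100% | 5.7% |
| Arms +0.2 and −0.2 at T2 and T3 (true effect) | 51 | 4.9% | 57% |
| Same | 375 | 5.3% | 100% |

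With Friedman run separately by arm under the no-effect profile, exactly one arm is significant in 45% of trials at 51 per arm.

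**Simulation 2.** Assumed correlation 0.65, 2,000 runs, repeated independently; ranges cover the repeats.
- No arm difference, common shift after T1, 46 per arm: rejection is about 6% with no shift, 15–16% at 0.1 SD, 49% at 0.2 SD, 85–86% at 0.3 SD and over 99% at 0.5 SD. At 375 per arm, a 0.2 SD shift gives 100%.
- True 0.237 SD difference split as ±0.1185 SD: 4–5% at 46 per arm and 5–6% at 375.
- Run separately by arm, 0.3 SD common shift, no true difference, 46 per arm: exactly one arm significant in 49–51%.

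**The case against.** The best case for the plan has four parts.

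1. *The rule is conditional.* The default is repeated-measures ANOVA, which does compare arms, and the article gives no distributional data. This stands as a limit on scope. But the article itself makes the switch depend on the data for all three outcomes, and a scale bounded at 20–80, such as the STAI, could well trigger it.

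2. *A between-arm route remains.* The Analysis section later describes multivariable linear regression with 95% confidence intervals. That step is foreseen only when baseline factors are substantially imbalanced, and it is not offered as the non-parametric route. It may never be run, so it does not repair the fallback.

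3. *The sizes rest on chosen scenarios.* This is fair. The correlation, trends and effect are not in the article. With control flat and intervention shifted by 0.237 SD, Friedman rejects in about 20% of trials at 46 per arm and 92–93% at 375, although it is still not testing the arm difference. If the pilot's 51 is deflated for non-consent as well (51/1.35 ≈ 38), the 0.3 SD common-trend figure falls to 77%. The one-arm-only pattern disappears at 375 per arm with a 0.3 SD trend (0%). Scores were also simulated as normal. However, Friedman uses only within-patient order, so applying any strictly increasing transformation to all scores leaves its rejection rates unchanged.

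4. *This is a pilot of 102 patients.* True, but effectiveness is a stated objective, the analysis rule is not confined to the pilot, and the false signal from a common trend is stronger at full size.

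**Conclusion.** The concern holds. The named fallback cannot test the between-arm hypothesis, because arm does not enter the Friedman statistic. That follows from the formula and needs no assumption.

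The practical size depends on the time trend, which the article does not give. At 46 per arm and correlation 0.65, the chance of a significant result with no arm difference runs from about 15% (0.1 SD common shift) to over 99% (0.5 SD). The chance of detecting a true 0.237 SD difference runs from about 5% (symmetric split) to about 20% (one arm flat). The fault takes effect only if normality is judged not to hold, but it then affects the initial comparison of whichever main outcomes switch. A possible unseen analysis plan does not excuse it, since the unsuitable test is named in the article itself. It should be corrected before any analysis.

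**What to change.** Delete the Friedman fallback. State one between-arm model that is kept whatever the normality check shows: a linear mixed model, or ANCOVA on the T2 and T3 scores adjusted for T1, with robust or bootstrap standard errors. As a sensitivity analysis, name a rank method that keeps the arm comparison, such as rank ANCOVA on T1 or a van Elteren (stratified Wilcoxon) test of change by diagnosis group, which matches the randomisation strata.

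Other choices would also cure the fault, for example a non-parametric factorial analysis of longitudinal data. The essential requirement is that any fallback includes arm. The cost is a change of wording in the analysis text; data collection, sample size and patients are unaffected.

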#### Sequence generation

Blocked randomisation will be performed with a block size of four by a computer generated random number list prepared by an investigator who has no clinical involvement in the trial. Stratification by primary cancer diagnosis group will also be carried out.

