### Measures

#### Anxiety

Anxiety will be measured using the trait anxiety version of the Spielberger's Trait Anxiety Inventory (STAI) and the Brief Profile of Mood States - Total Mood Disturbances Score (POMS-TMDS) [35-37].

The STAI was developed as a tool for investigating anxiety in normal adults, but has been used extensively for assessing anxiety in cancer patients [10,11,21,33]. The scale consists of 20 questions yielding a measure of state anxiety (S-Anxiety) which assesses how a patient feels generally. An extra 20 questions refer to trait anxiety (T-Anxiety) which refers to individual differences in "anxiety-proneness" [35]. The STAI demonstrated good psychometric properties [35]. Reliability has been substantiated by means of test-retest correlations (r = 0.65-0.86) and Cronbach's alpha (median coefficient of 0.90). Scores on the scales can range from 20-80, with higher scores indicating more symptoms of anxiety [21].

The POMS-TMDS is a shorter version of the 65 item Profile of Mood States (POMS) [37]. It consists of 11 items that yield a total mood disturbance score that correlates highly (r = 0.93) with the longer POMS which has been utilised extensively for the cancer population [10,11,33,38]. Reliability and validity testing has been carried out successfully in patient with cancer [39]. Permission for use has been granted by the author.

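### Covariates are chosen by observed baseline imbalance, with no threshold and no fixed primary estimate, instead of prespecifying the T1 score and the stratification factor

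*Protocol article*

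**What the plan says.** The Analysis section of the protocol article sets out a sequence.

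1. Mean scores on the three scales "will be compared initially across intervention and control groups using ANOVA (repeated measures) to analyse the effect between groups over time". No covariates are named.
2. "Success of randomisation will then be considered by cross-tabulating trial group with the range of factors".
3. "Any found to be in substantial imbalance will be included in multivariable linear regression models, via forced entry, to adjust the crude means". The adjusted means are to be reported with 95% confidence intervals.

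There is no list of candidate factors, no definition of substantial, and no statement of which estimate is the main result.

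Three other places bear on this:

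- Sequence generation: "Stratification by primary cancer diagnosis group will also be carried out", with blocks of four. Diagnosis group does not appear in the Analysis section.
- Data collection: questionnaires at T1, T2 and T3, "which will measure patients' self-efficacy (CASE) and anxiety (STAI and POMS) at the three time points". A T1 score therefore exists for every outcome.
- Allocation concealment/implementation: after consent comes the allocation telephone call. "Subsequently, baseline data will be collected". The Blinding/masking section says that patients cannot be blinded.

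**The concern.** A covariate is worth including because it predicts the outcome. Whether it differs between arms after proper randomisation is a matter of chance. A rule keyed to observed imbalance selects on the wrong property, and it does so after the outcome comparison has been made. Without a threshold, two analysts could reach different covariate sets from the same data.

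Three things are at stake:

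- **The estimate is not fixed.** A crude and an adjusted result will both exist, and the adjusted one depends on the data.
- **Precision.** A prognostic factor that happens to be balanced is left out, and its explained variance stays in the error term.
- **The stratifier.** Stratified blocks of four are meant to balance diagnosis group, so the screen would almost never pick it. If diagnosis is prognostic, leaving it out makes the standard errors too large.

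**Working it through.** **The plan's own figure.** The section Sample size and power has the nearest one: "A sample size of at least 375 in each arm of the study would be sufficient to achieve a power of 90% using 95% of" (the quote breaks off at the confidence level). It cannot be reproduced, because no difference or SD is given. Inverting it (two-sided alpha 0.05, 1:1) gives the implied detectable difference: (1.960 + 1.282) × √(2/375) = 0.237 SD. This is a back-calculation, not a protocol figure.

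**Correlation.** The Anxiety section says "Reliability has been substantiated by means of test-retest correlations (r = 0.65-0.86"). Using this range for the correlation between T1 and follow-up in this trial is an assumption. No value is given for POMS or CASE-cancer.

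**1. Gain from T1 as a covariate.** Take equal SDs at each visit, with the variance of a single follow-up score set to 1:

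- change from T1: 2(1 − r)
- covariate adjustment for T1 (ANCOVA): 1 − r²
- ratio of ANCOVA to change: (1 − r²) / [2(1 − r)] = (1 + r)/2

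| r | Change | ANCOVA | Ratio | Extra patients for change |
|---|---|---|---|---|
| 0.65 | 0.70 | 0.5775 | 0.825 | 1/0.825 − 1 = 21% |
| 0.86 | 0.28 | 0.2604 | 0.93 | 1/0.93 − 1 = 7.5% |
| 0.50 (assumed) | 1.00 | 0.75 | 0.75 | 33% |
| 0.30 (assumed) | 1.40 | 0.91 | 0.65 | 54% |

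If the 375 per arm had been planned on change, ANCOVA would need 375 × 0.825 = 310 (rounded up) at r = 0.65, or 375 × 0.93 = 349 at r = 0.86.

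**2. The same in the pilot.** With 51 per arm less 10% loss, about 46 are evaluable. The 95% half-width is 1.96 × √(2/46) × √variance = 0.409 × √variance:

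- r = 0.65: change 0.342 SD, ANCOVA 0.311 SD
- r = 0.86: change 0.216 SD, ANCOVA 0.209 SD

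**3. If the group main effect is tested instead.** Averaging T1, T2 and T3 dilutes an effect δ present at T2 and T3 to 2δ/3. Under compound symmetry the variance is (1 + 2r)/3, which is 0.767 at r = 0.65 and 0.907 at r = 0.86. At 375 per arm and δ = 0.237 SD, power is 69% and 62%. ANCOVA on one follow-up score gives about 99% and nearly 100%.

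**4. What the imbalance rule does.** The simulation used 20,000 runs per setting and one covariate correlated r with the outcome. Adjustment was made only if the baseline difference had p < 0.05, which is an assumed trigger because the protocol gives none. Otherwise the follow-up score was compared unadjusted. The covariate entered in about 5% of trials.

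| n per arm | r | SD of estimate: never / by rule / always adjusted | Type I error by rule |
|---|---|---|---|
| 51 | 0.65 | 0.197 / 0.186 / 0.151 | 0.037 |
| 51 | 0.86 | 0.198 / 0.176 / 0.102 | 0.027 |
| 375 | 0.65 | 0.073 / 0.069 / 0.056 | 0.038 |
| 375 | 0.86 | 0.073 / 0.065 / 0.037 | 0.025 |

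Always adjusting kept type I error near 0.05. The rule recovers little of the available precision and is conservative. These r values are as strong as a repeat of the same scale; for weaker factors the loss is smaller.

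**5. The stratifier.** If the blocks of four run within diagnosis groups, an unfinished block leaves the arms at most two patients apart in any group at randomisation. No figure links diagnosis to the scores, so the effect of omitting it cannot be sized.

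**The case against.** The strongest reply is that T1 is already used. All three scales are measured at T1, and the first analysis is a repeated-measures ANOVA of the group effect over time, most naturally read as group-by-time. That stands, and it limits the size of the point.

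A reader might infer that T1 is discarded, and so set ANCOVA against a T2-only comparison. The pilot half-width would then fall from 0.41 SD to 0.31 or 0.21 SD, and power for 0.237 SD would rise from 21% to between 32% and 61%. The protocol describes no T2-only analysis, so those contrasts do not measure the cost of its plan. Nor does it say that T1 scores are left to the imbalance screen; the factors screened read back to the risk factors collected at baseline.

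A second reply is that an article may leave the full model to an analysis plan. That is fair for mere silence about T1 or diagnosis group as covariates, and such silence is not the finding. The imbalance rule, however, is written down. An analysis plan would have to overturn it, not just fill a gap.

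A third reply is that no false-positive harm is shown. This is correct for the setting simulated: type I error was below nominal.

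**Conclusion.** The point holds as a fault in a stated rule. Choosing covariates by chance imbalance, with no threshold and no named primary estimate, makes the adjusted result data-driven and wastes precision. The rule would almost never bring in the factor used to stratify.

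The size is modest if the test is the group-by-time contrast, simplified here to change from T1 to one follow-up: about 21% to 7.5% more patients than ANCOVA, provided the general STAI reliability range carries over to this trial. The cost is larger if r is lower, or if the group main effect over all three visits is what is tested; the protocol does not say explicitly which contrast decides. The loss from omitting diagnosis group cannot be quantified and depends on diagnosis being prognostic. The documents do not support a claim of inflated type I error, or one that the baseline score is ignored.

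**What to change.** - For each scale, prespecify one primary model: T2 and T3 scores as outcomes, with arm, time, arm-by-time, the T1 score of that scale and primary cancer diagnosis group as terms. Report the adjusted difference with its 95% confidence interval as the main result, and state whether it is the difference at T2, at T3 or their average.
- Use the baseline table for description only. Delete the imbalance-triggered adjustment or move it to sensitivity analysis.
- Have T1 completed before allocation is disclosed. As written, baseline collection follows the allocation call and patients are unblinded, so knowledge of the arm could affect T1 and weaken it as a baseline covariate. The planned ANOVA shares this weakness.

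The first two changes are wording only, since the T1 scores and diagnosis group are already collected. The third changes the order of recruitment steps but needs no new data. The pilot is the time to settle all three, before the full trial inherits the rule.
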